#### Ensuring reproducibility and reliability of measurements of outcome

We will use reliable and valid measures of attitudes to EBP that have been used with the studied clinical disciplines [44,76,80,81]. CSR will be performed by two independent raters and checked for initial reliability.

#### Control of biases relating to (loss to) follow-up

We will use the following measures to ensure minimal loss to follow-up: (1) enrollment/consent will emphasize committing to the entire trial period and will exclude clinicians who cannot commit to the study for 18 months, (2) contact information will be updated at each study interval, and (3) response burden has been kept low. Burden is reduced since brief measures are embedded in the intervention; the total time required for extra questionnaires is relatively low and will be time distributed. The system will initiate regular reminders until the data collection is complete (or the participant withdraws consent).

#### Compliance

Compliance is one of our monitored variables. When participants fail to use an intervention, they are classified in some studies as noncompliant. We view lack of use as a failure of the intervention to meet participant needs. Thus, participants who do not use this service will not be classified as noncompliant or dropouts. Dropouts will be defined as participants who inform us that they no longer wish to participate in the study follow-up process. These participants will not be denied access to the intervention, and we will request permission to continue to use data from the embedded tracking of usage. Each participant will receive a $45 gift card upon completion of at least three survey assessments: baseline, one follow-up (at 3, 9, or 15 months), final assessment. Participants who complete the CSR or the search skills assessment will receive an additional $20 gift card as honorarium for time volunteered.

#### Planned data analyses

Quality checking of primary and secondary outcome data will be performed by re-entry of 100 cases and checking concordance. Descriptive statistics, including frequencies, means, and standard deviations, will be calculated and data displayed graphically for all study variables as a means of exploring data distributions. The data for all outcome measures will be analyzed to ensure that they meet the statistical assumptions necessary to use parametric statistics. Transformations may be considered if necessary to meet test assumptions. To test our main research question, we will use general, linear mixed-effects models [82] for repeated measurements over time to explore the relationship among the use/behavior scores, comparing the effects between professional groups and intervention types. The models will be fitted for the outcome scores over time as a function of the between-participant (profession/intervention) and within-participant (time) variables. Utilizing a mixed-model approach allows us to account for the dependence between outcome measurements taken over time from the same participant. The structure of the variance-covariance matrix, which dictates the dependence between measurements in the fitting of the model, will be chosen based on standard criteria in statistics. *Post hoc* pairwise comparisons of the two treatment arms at different time points will be done using multiple comparisons with adjustment to the Type I error rate. Type I error will be set to 5% (*i.e.*, α = 0.05) for all the calculation of the confidence intervals and performing the various hypothesis-testing procedures. Type I error will be adjusted accordingly for multiple comparisons. Standard diagnostic tools will be used to assess any of the model fittings. An intent-to-treat analysis will be employed—those who do not participate will be included in the analysis in their original group. No interim analyses are planned since there are no safety issues and we wish to ensure full power for both primary and secondary analyses.

We also plan to analyze difference in professional attitudes, evidence access, and use. We have powered our study to allow this analysis. Our subgroup analyses will also describe differences in types of evidence accessed. Our group previously determined that physicians prefer systematic reviews to primacy studies and that access was better through peer-reviewed journals than through Cochrane Collaboration [83]; we will now extend this type of analysis to look at evidence accessed across professions by comparing the types of primary studies (clinical, basic science; quantitative/qualitative), content (prognosis, diagnosis, clinical measurement, treatment effectiveness/outcomes, economic, etiology), and journals (disciplinary/interdisciplinary/other discipline).

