**Methods:**

Physicians, nurses, occupational/physical therapists, and psychologists (n = 670) will be randomly allocated in a crossover design to receive a pain evidence resource in one of two different ways. Evidence is extracted from medical, nursing, psychology, and rehabilitation journals; appraised for quality/relevance; and sent out (PUSHed) to clinicians by email alerts or available for searches of the accumulated database (PULL). Participants are allocated to either PULL or PUSH + PULL in a randomized crossover design. The PULL intervention has a similar interface but does not send alerts; clinicians can only go to the site and enter search terms to retrieve evidence from the cumulative and continuously updated online database. Upon entry to the trial, there is three months of access to PULL, then random allocation. After six months, crossover takes place. The study ends with a final three months of access to PUSH + PULL. The primary outcomes are uptake and application of evidence. Uptake will be determined by embedded tracking of what research is accessed during use of the intervention. A random subset of 30 participants/ discipline will undergo chart-stimulated recall to assess the nature and depth of evidence utilization in actual case management at baseline and 9 months. A different random subset of 30 participants/ discipline will be tested for their skills in accessing evidence using a standardized simulation test (final 3 months). Secondary outcomes include usage and self-reported evidence-based practice attitudes and behaviors measured at baseline, 3, 9, 15 and 18 months.

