## Methods/design

The trial is a crossover randomized controlled trial (RCT) with repeated baseline and follow-up measurements (Figure 1). The interventions are two different types of access to pain research evidence for four different types of professionals involved in pain management. The trial will begin with a three-month (repeated) baseline, during which average participant use of the standard PULL resource will be monitored. Participants will then be randomly allocated to either receive PUSH + PULL or continue to use the PULL resource. After six months, participants will cross over to the alternate intervention for an additional six months. To complete the trial, both groups will finish with three months of PUSH + PULL access. The repeated baseline period provides more stable estimates of participants’ access prior to randomization. The rationale for the crossover design is that it will maximize our statistical efficiency, increasing the precision of effect estimates. This is particularly important for our subgroup (profession) estimates; it will also provide better control of unknown potential confounders. The main potential drawback of a crossover design occurs if the “wash-out” is incomplete. While we will have control of the intervention delivery, the exposure to email alerts may affect use of the pull resources; therefore, we will test for order effects. The study received Ethics Approval from the McMaster University Research Ethics Board.

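### The main model classes intervention as a between-participant factor, although in this crossover every participant receives both conditions and the treatment effect lies within participants

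*Protocol article*

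**What the plan says.** Methods/design describes a two-sequence crossover: "The trial is a crossover randomized controlled trial (RCT) with repeated baseline and follow-up measurements". Everyone has three months of PULL before allocation, then six months on the allocated condition. "After six months, participants will cross over to the alternate intervention for an additional six months". Finally, "To complete the trial, both groups will finish with three months of PUSH + PULL access". The Randomization section adds that the switch at nine months is automatic. The stated reason for this design is that "it will maximize our statistical efficiency, increasing the precision of effect estimates", and the article singles out the profession estimates as needing that gain.

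Planned data analyses then specifies linear mixed-effects models for the main research question, fitted "as a function of the between-participant (profession/intervention) and within-participant (time) variables". Time is the only within-participant variable listed. Arm contrasts by visit, which carry a post hoc label, appear next: "pairwise comparisons of the two treatment arms at different time points will be done using multiple comparisons with adjustment to the Type I error rate". The section names no period term and no treatment term that changes over time. Methods/design does promise a test for order effects, because alerts may influence later use of the PULL resource.

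**The concern.** The classification does not match the design. A variable that is constant within a participant in a two-sequence crossover is the sequence to which that participant was allocated. Both sequences receive the same total amount of each condition, so a sequence main effect does not estimate what PUSH adds to PULL. In such a design the sequence term is where carryover and order effects show up, so the model as worded would give the label of intervention to the quantity that the order test is meant to examine.

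Two things are at stake. An analyst who follows the sentence literally could report the wrong coefficient as the answer to the main question. An analyst who instead relies on the post hoc visit comparisons uses between-person contrasts and loses the precision that justified the crossover.

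**Working it through.** **Inputs.** From the article: the condition sequence (Methods/design); KABQ visits at 0, 3, 9, 15 and 18 months (Timing of measures); effect size 0.40, two-tailed alpha 0.05 and 80 per group (Sample-size calculations). Assumed, because the article gives no value: within-person correlation ρ, shown over a range; carryover c; outcome SD of 1.

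**The plan's own figure.** 80 × 2 × 4 = 640 is right arithmetically. The 80 itself is not reproduced from the two-tailed inputs: 2(1.960 + 0.842)²/0.40² gives 99, while a one-sided test gives 78. The argument below does not depend on this; 80 per sequence is used as the planned number.

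**Step 1: exposure.** Condition at each visit (1 = PUSH + PULL):

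| Month | 0 | 3 | 9 | 15 | 18 |
|---|---|---|---|---|---|
| PUSH first | 0 | 0 | 1 | 0 | 1 |
| PULL first | 0 | 0 | 0 | 1 | 1 |
| Arm difference for constant effect d | 0 | 0 | +d | −d | 0 |

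In months of PUSH + PULL, the PUSH-first sequence has 6 + 3 = 9 and the PULL-first sequence 6 + 3 = 9.

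**Step 2: sequence main effect.** With equal weights it is (0 + 0 + d − d + 0)/5 = 0. For d = 0.40 the expected generalised least squares value is 0.000 under compound symmetry and under AR(1) by visit. Under a continuous-time autoregressive structure (correlation 0.9 per month) it is at most 0.017. If PUSH carries over by c into the PULL period of the PUSH-first arm, the term becomes c/5 over five visits under compound symmetry (0.02 to 0.08 for c = 0.1 to 0.4), or c/2 on months 9 and 15 alone (0.05 to 0.20).

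**Step 3: simulation.** 640 participants, d = 0.40, ρ = 0.5, no carryover, 60 runs.
- Intervention coded as allocated group: mean estimate −0.007 (SE 0.061), significant in 5% of runs.
- Intervention coded as current condition, with visit and sequence: mean estimate 0.397 (SE 0.040), significant in 60 of 60.
- Group-by-time model: arm difference +0.39 at 9 months and −0.41 at 15 months.

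**Step 4: precision in one profession, 80 per sequence.**
- Single-visit arm comparison: SE = √(2/80) = 0.158. Power for 0.40 is Φ(0.40/0.158 − 1.96) ≈ 0.72 before any multiplicity adjustment.
- Crossover contrast, half the difference between the 9- and 15-month arm differences: SE = ½√[2(1 − ρ) × 2/80] = √[(1 − ρ)/80]. At ρ = 0.5 this is 0.079.
- Ratio of the two: √[2/(1 − ρ)], which is 1.41 at ρ = 0, 1.58 at 0.2, 2.00 at 0.5 and 3.16 at 0.8.

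**Step 5: pooled over professions, about 320 per arm.** The single 9-month comparison has SE = √(2/320) = 0.079 and power Φ(5.06 − 1.96) ≈ 0.999. With a Bonferroni adjustment for five visits it is Φ(5.06 − 2.58) ≈ 0.99.

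**Step 6: what carryover does to the crossover contrast.** With carryover c the 15-month arm difference is c − d, so the contrast becomes [d − (c − d)]/2 = d − c/2. The 9-month comparison is unaffected by c.

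**The case against.** The best defence is that the article never says the main question is tested by an arm main effect averaged over visits. It models scores over time and then compares arms at individual time points, which suggests that arm and time interact. In a two-sequence crossover, allocated group is sequence and visit is period, so the group-by-time term contains the treatment effect. With 80 per arm and d = 0.40 under compound symmetry, the four-degree-of-freedom interaction test has power of about 83% at ρ = 0 and 99% at ρ = 0.5. The crossover contrast of Step 4 can be taken from the same fitted model. This stands: the effect is recoverable. But the interaction is not named as the test, and the visit contrasts are called post hoc.

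Several stronger readings are therefore not supported:
- A reader might infer that the main test has power equal to alpha. That follows only if the sequence main effect is taken as the test, which the article does not say.
- A reader might take the term to be exactly zero by construction. It is zero only in expectation and under the conditions in Step 2, and the article itself anticipates that alerts could affect later PULL use.
- A reader might take the intent-to-treat sentence, "those who do not participate will be included in the analysis in their original group", as defining how treatment is coded. It concerns people who do not participate; the point rests on the between-participant wording alone.
- A reader might conclude that the post hoc comparisons leave the whole trial underpowered. Step 5 shows otherwise for the pooled comparison.

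An article may leave exact model terms to an analysis plan. That does not cover a classification that is stated and conflicts with the design.

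**Conclusion.** The point holds as a misstatement of the main analysis. Intervention is a within-participant factor in this trial, and the model sentence puts it on the other side. Coded as worded, its main effect is about zero in expectation with equal period effects, no carryover and symmetric weighting. Without those conditions it is a small quantity that does not estimate the benefit of PUSH.

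The precision loss matters mainly for the profession estimates: a single-visit comparison has 1.4 to 3.2 times the standard error of the crossover contrast for ρ from 0 to 0.8, and twice at 0.5. These figures assume compound symmetry, unit SD and 80 per sequence. The main question pooled over professions is not short of power at 9 months.

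The point concerns outcomes measured in both periods. Chart-stimulated recall, done only at baseline and nine months, does not span the switch, and a between-participant factor suits it.

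**What to change.** Reword the model in Planned data analyses. State intervention as a time-varying within-participant factor, the current condition in months 3–9 and 9–15, or equivalently state the sequence-by-period contrast. Include terms for period, sequence, profession and intervention by profession, and a participant random effect. Name this contrast as the single prespecified primary test for each repeated outcome, in place of the post hoc visit comparisons. Leave months 15–18 out of the intervention contrast, since both arms then have PUSH + PULL.

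Keep the planned order or carryover test and attach it to the sequence term. Because carryover would shift the crossover contrast by c/2, report the 9-month between-arm comparison, which is free of carryover, as a sensitivity analysis.

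The cost is analysis wording only; data collection, visits and sample size are unchanged.

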### Steering committee

The Steering Committee will consist of the four investigators. The study coordinator will prepare a monthly report, detailing the accrual rate, loss to follow-up, withdrawals, and compliance with study protocols. Since this trial does not directly involve patients, there is no need for a Data Safety Monitoring Committee.

### Trial status

We have enrolled more than 70% of the sample target. More than 60% of the participants have reached the nine-month milestone (crossover).

## Discussion

This trial should provide unique information on evidence-access skills and professional differences in use of evidence. We expect to demonstrate the effectiveness of push-out targeted evidence (Pain PLUS) and to move the intervention into open access upon trial completion. We expect that some differences in evidence access and application will occur across professional groups, both in terms of types of pain interventions and types of research that are accessed.

It is our intent to ensure this intervention becomes open access to have ongoing impact. We believe this trial will inform our understanding on how to best deliver evidence to clinicians across a variety of professions dealing with pain. Sustainability of KT interventions is a critical issue area. As our findings emerge, we will deal with sustainability issues. Since evidence updates have been created for specific disciplines, including physicians, nurses, and rehabilitation professionals, it may be that folding in a pain resource into these existing resources would be the optimal method to ensure sustainability. Conversely, pain stakeholders may prefer a customized resource. A variety of pain resources are being developed, and strategies to share these across stakeholders are just emerging in stakeholder discussions. This may form an opportunity to tailor the knowledge from this study to emerging resources. Using the knowledge about what pain evidence exists, is accessed, and valued across professions will allow us to develop a pain knowledge strategy. The sustainability plan will be designed to maximize uptake of pain knowledge in a sustainable manner.

One of the benefits of this study is the ability to compare the evidence accessed by different professions when dealing with the same issue. We will use a descriptive approach to convey these differences by classifying the type of pain, the type of clinical questions, and the type of research design of these studies to convey if different types of evidence are valued by different professions. We anticipate, for example, that nurses and therapists might access more qualitative research, whereas physicians might access more RCTs on drug interventions. Psychologists are being included for the first time in this type of intervention, and their information behaviors are relatively unstudied. We expect that this information might help us understand if evidence scanning and filtering needs to be adjusted across professions. For example, decisions about how to filter qualitative studies may be more challenging than are such decisions in quantitative research.

We also acknowledge that the information resources that are available to knowledge users are rapidly expanding. Resources vary in their delivery, quality, customization, source content, and format of information. Knowledge users may become overwhelmed with information resources or stick with ones they have become comfortable with, irrespective of the quality of the information. It may not be clear to end users that the evidence-filtering process used in Pain PLUS protects them against low-quality information. Further, as clinicians often value advice about clinical decision making in actual cases, or implementation issues, they may be drawn to information resources that focus on these rather than the primary or synthesized research available. Since information is always in competition with other information, we cannot be certain that Pain PLUS will win in this competition.
